### Participant timeline {13}

The participant timeline can be found in Table 1.

**Table 1 Tab1:** Study table

	Screening (Day − 1)	Enrolment (Day 0)	Day 1	Day 2	Day 3–6	Day 7	Day 8–13	Day 14	Day 21	Day 28	Month 2	Month 3	Month 4	Month 5	Month 6	Day of recurrence
Treatment																
CQ	X	X	X													
14 day PQ 0.25 mg/kg BW		X	X	X	X	X	X									
7 day arm PQ 0.50 mg/kg BW		X	X	X	X											
Procedures																
Malaria RDT for *P. vivax*	X															X
Dengue NS1 RDT	X															X
Physical examination including temp		X	X	X		X		X	X	X	X	X	X	X	X	X
CBC and LFT		X														X
G6PD UVS	X															
G6PD Biosensor	X															
Microscopy	X	X	X	X		X		X	X	X	X	X	X	X	X	X
Hb by Hemocue		X	X	X		X		X	X	X	X	X	X	X	X	X
Urine pregnancy test	X															X
Physical examination of urine			X	X		X										X
DBS		X														X
AE/SAE		X	X	X	X	X	X	X	X	X	X	X	X	X	X	X

### Sample size {14}

The 0.25mg/kg/day × 14 days regimen of primaquine is associated with ~13% recurrence rate of vivax malaria [12]. The present study will assess if 0.50 mg/kg/day for 7 days will have an equivalent recurrence rate within a margin of 10%. A sample size of 200 per group, assuming a 30% loss to follow-up at 5% significance will provide 68% power to detect this difference. Accordingly, we have decided on 200 patients at each site (100 in each arm), 400 in total.

### Recruitment {15}

#### Trial participants

Male and female patients over the age of 16 years, with uncomplicated vivax malaria presenting to a participating centre will be enrolled into the study if they fulfil the eligibility criteria. Patients will be recruited at established hospital sites in malaria-endemic areas with large catchment areas and sufficient malaria patient load. Patients will be recruited for a period of 6 months and it is aimed to recruit an equal number of participants at both sites.

## Methods: assignment of interventions

### Sequence generation {16a}

Patients presenting with *P. vivax* malaria, who are G6PD normal and meet the other eligibility criteria will be allocated randomly to one of two arms. The allocation ratio of is 1:1, and randomisation will be performed using computer-generated random numbers. The randomisation sequence will be generated by an independent statistician who is not involved in the enrolment or assignment of participants. Information on block size has not been shared with the team recruiting patients.

### Concealment mechanism {16b}

To ensure allocation concealment, the randomisation list will be securely stored in the study database by an independent team member with no direct involvement in patient recruitment or assessment. The next allocation will remain concealed until the screening process is complete, and the patient qualifies for enrolment in the study.

### Implementation {16c}

Enrolment and assignment of participants will be done by qualified study staff who have received delegation by the study PI to conduct these tasks. The allocation sequence, generated by the independent statistician, will be kept confidential and will not be accessible to the study staff involved in participant enrolment and assignment. The study staff will only have access to the allocation information at the time of participant assignment.

## Assignment of interventions: blinding

### Who will be blinded {17a}

Not applicable, as neither participants nor study staff will be blinded to the allocation.

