### Procedure for unblinding if needed {17b}

Not applicable, as the study is not blinded, therefore no procedures for unblinding are required.

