#### Microscopic blood examination

Specimens will be labelled anonymously (screening number or study number, day of follow-up, date). A fresh Giemsa stain dilution will be prepared at least once a day and possibly more often, depending on the number of slides to be processed. Giemsa-stained thick and thin blood films will be examined at a magnification of 1000× to identify the parasite species and to determine the parasite density.

Two blood slides per patient will be obtained: Both thick and thin blood smear on the same slide. One slide will then be stained rapidly (10% Giemsa for 10–15 min) for initial screening by confirming the presence or absence using the thin smear, while the second slide will be retained. If the patient is subsequently enrolled, the second slide will be stained more carefully (e.g. 6% Giemsa for 45–60 min), and slower staining will also be used for all slides obtained at follow-up visits. The study number of the patient, the date and the day of follow-up will be recorded either on the frosted edge of the slide or on the glass with a permanent glass pen.

On the slow stained slides, thick blood smear for initial screening will be used to count the numbers of asexual parasites as well as sexual (gametocytes) parasites. Thin smear will be used for species identification and parasite stage determination.

The second thick blood smear will be used to calculate the peripheral parasite density, by counting the number of asexual parasites per 500 white blood cells with a hand tally counter. Parasite density, expressed as the number of asexual parasites per μl of blood, will be calculated by dividing the number of asexual parasites by the number of white blood cells counted and then multiplying by the actual white blood cell density (from the CBC reports on Day 0 for enrolled patients).$$\textrm{Parasite}\ \textrm{density}\ \textrm{per}\ \upmu \textrm{l}=\frac{\textrm{Number}\ \textrm{of}\ \textrm{parasites}\ \textrm{counted}\times \textrm{Actual}\ \textrm{WBC}\ \textrm{density}}{\textrm{Number}\ \textrm{of}\ \textrm{leukocytes}\ \textrm{counted}}$$

The same technique will be used to quantify parasite density on each subsequent blood film. A blood slide will be considered negative when examination of 200 high power fields (HPFs) reveals no asexual parasites.

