In addition, 100 fields of the second thick film will be examined to exclude mixed infections; in case of any doubt, the thin film will be examined for confirmation. If examination of the thin film is not conclusive, the patient will be excluded from the analysis after complete treatment and follow-up.

Two qualified microscopists will read all the slides independently, and parasite densities will be calculated by averaging the two counts. Blood smears with discordant results (differences between the two microscopists in species diagnosis, in parasite density of > 50% or in the presence of parasites) will be re-examined by a third, independent microscopist, and parasite density will be calculated by averaging the two closest counts. This will be done on days − 1, 0, 1, 2, 7, 14, 21, and 28 and monthly until month 6 and the day of recurrence.

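### The protocol leaves all study staff unblinded and does not exempt the slide readers, whose readings decide recurrent parasitaemia; masking them would be cheap

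*Protocol article*

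**What the plan says.** Who will be blinded {17a} answers the item directly: "neither participants nor study staff will be blinded to the allocation". Procedure for unblinding if needed {17b} confirms it: "Not applicable, as the study is not blinded, therefore no procedures for unblinding are required". Neither section makes an exception for laboratory readers.

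Microscopic blood examination describes how slides are handled. On labelling: "Specimens will be labelled anonymously (screening number or study number, day of follow-up, date". On reading: "Two qualified microscopists will read all the slides independently". Slides on which the two disagree about species, density or the presence of parasites are "re-examined by a third, independent microscopist". The same section has a rule for suspected mixed infection: "If examination of the thin film is not conclusive, the patient will be excluded from the analysis after complete treatment and follow-up".

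The efficacy endpoint rests on these readings, but the article describes it in two ways. The Abstract gives any P. vivax parasitaemia at 6 months, and Statistical methods {20a} analyses time to first recurrent parasitaemia. Outcomes {12} makes symptomatic P. vivax malaria primary, with recurrence-free status defined by blood films, and places symptomatic plus asymptomatic recurrence among the secondary outcomes.

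**The concern.** Open-label treatment is not the fault: regimens of 7 and 14 days without placebo cannot easily be hidden from patients or treating staff. The concern is that the unblinded status is stated for all staff, and so covers the people who read the outcome.

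Whether a low-density film is positive is partly a judgement. The protocol accepts this by providing for disagreement on whether parasites are present at all. A reader who knows the arm may search or call slightly differently. Two readers reduce random error, but they do not remove a bias that both share because both know the arm.

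The trial is a non-inferiority comparison, so under-calling in the 7-day arm, or over-calling in the 14-day arm, pushes the result towards a false claim of non-inferiority. The opposite pattern could cost a true one.

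The mixed-infection rule is a second point of exposure. It removes a patient from the analysis on a microscopy reading, and the protocol does not say that the reading is masked or when the decision is taken.

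**Working it through.** **Does any section mask the readers?**

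| Section | What it provides | Does it mask readers to arm? |
|---|---|---|
| Who will be blinded {17a}; Procedure for unblinding {17b} | No one is blinded | No, and no exception |
| Concealment mechanism {16b} | The next allocation is hidden until the patient qualifies; the list is held by someone outside recruitment and assessment | Protects the sequence before assignment only |
| Implementation {16c} | Staff see the allocation at assignment | No |
| Microscopic blood examination, labels | Number, day and date; no arm | Lowers the risk, but the number can be linked to the arm |
| Microscopic blood examination, readers | Two independent readers and a third | Independent of one another; not said to be unaware of the arm |
| Participant timeline {13}, Table 1 | Slides on the same days in both arms | Helpful: the day on the label does not reveal the arm |
| Study procedures for the main study, unscheduled visit | Smear read at once at the enrolling health centre | No |

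**Illustration of sensitivity.** The protocol has no figure on reading bias to reproduce. The shift *b* below is an assumption.

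Inputs from Sample size {14}: control recurrence 13%, margin 10 points, 200 per arm with 30% loss. Evaluable per arm = 200 × 0.70 = 140. That section gives 5% significance without stating sides; a one-sided 2.5% test is assumed here.

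*Type I error.* Set the true 7-day risk at the margin, 13% + 10% = 23%.

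SE = √[(0.13 × 0.87 + 0.23 × 0.77) / 140] = √(0.2902 / 140) = 0.0455

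Error with a shift *b* in favour of the 7-day arm = Φ(*b* / 0.0455 − 1.96)

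| Assumed shift | Patients of 140 | Argument of Φ | One-sided error |
|---|---|---|---|
| 0 | 0 | −1.96 | 2.5% |
| 1 point | 1.4 | −1.74 | 4.1% |
| 2 points | 2.8 | −1.52 | 6.4% |
| 3 points | 4.2 | −1.30 | 9.7% |

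A cross-check in whole patients, with the SE recomputed each time, agrees in scale. If 1, 2 or 3 true recurrences in the 7-day arm alone are read as negative, the error is about 3.6%, 5.0% or 7.0%.

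*The other direction.* Let both true risks be 13%. SE = √(2 × 0.13 × 0.87 / 140) = 0.0402. Power with a shift *b* against the 7-day arm = Φ((0.10 − *b*) / 0.0402 − 1.96). This is 70% at *b* = 0, 61% at 1 point, 51% at 2 points and 41% at 3 points, holding the SE fixed.

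**The exclusion rule.** The sentence before it concerns the second thick film, examined to rule out mixed infection. The section describes the second slide as one kept back at screening and stained carefully once the patient is enrolled. The trigger is therefore most naturally an enrolment slide. Its careful reading can come after allocation. When the exclusion decision is taken, relative to the outcome, is not stated.

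**The case against.** The best defence is that the process is already fairly well protected. Labels omit the arm, slide days match between arms, every slide is read twice, and disagreement on the presence of parasites goes to a third reader. A biased call has to survive all of that. The randomisation list is kept away from assessors, and laboratory access rules are detail that an article often leaves to the full protocol or to operating procedures. Much of this stands: the risk is reduced, and nothing shows that readers will know the arm. The last argument does not answer the point, because the article takes up the blinding item and answers it without exception. If the readers are in fact masked, {17a} is wrong as written.

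A reader might also infer four stronger things that the documents do not support.

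- *That patients are excluded once arm and outcome are known.* The rule appears to concern enrolment slides, and it says that the patient completes treatment and follow-up, not that the decision waits for them. Only the timing is open.
- *That asymptomatic low-density calls bear on the primary endpoint under every definition.* They do under the Abstract and {20a}. Under Outcomes {12} the primary outcome is symptomatic, so microscopy supplies only the parasitological part.
- *That the bias can be sized by adding a per-slide difference over the follow-up visits.* No such difference is given, errors need not all run one way, and a positive missed at one visit can be caught at the next.
- *That masking is free.* No costs or staffing are given, roles must be separated, and unscheduled smears are read immediately at the site.

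**Conclusion.** The point holds in a limited form. The protocol states that no study staff are blinded and does not exempt the microscopists who determine recurrent parasitaemia. The existing safeguards reduce the risk of arm-dependent reading without masking the readers.

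The size is unknown. The 4.1%, 6.4% and 9.7% figures show only how sensitive the non-inferiority conclusion would be to shifts of 1, 2 and 3 points. They rest on 140 evaluable per arm, true risks of 23% and 13%, a one-sided 2.5% test and a normal approximation. A shift may be absent or run the other way. What the illustration supports is that a few patients classified differently by arm would matter, so a cheap protection is worth having.

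**What to change.** 1. Amend Who will be blinded {17a}: treatment remains open-label, but the two slide readers and the third reader have no access to allocation or dosing records. Align {17b} with this.
2. State that any unscheduled smear read immediately for care is classified for the endpoint by the masked double reading. Microscopic blood examination already requires that reading on the day of recurrence, so immediate reading for care is unaffected.
3. State in Microscopic blood examination that the mixed-infection exclusion is decided from the enrolment slides, by masked readers, before outcome data are linked.

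The cost is wording, modest access control and separation of the reading role from home visits and dosing at two sites. No extra readers or procedures are expected, since labels already omit the arm and double reading is already planned. The documents give no staffing figures, so the sites should confirm this.

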### Procedure for unblinding if needed {17b}

Not applicable, as the study is not blinded, therefore no procedures for unblinding are required.

## Data collection and management

### Plans for assessment and collection of outcome {18a}

Data will be collected as described below and in the study Table 1. All study data will be recorded on standard Case Report Forms (CRF) and entered into a REDCap database, a GCP-compliant data management system.

#### Pre-study

Only patients with G6PD activity ≥30% of the adjusted male median (AMM) as determined by UV spectrophotometry will be eligible for enrolment into the main trial. In order to determine 100% G6PD activity at each site, a total of 30 adult male healthy volunteers from the health facility will be sampled. A separate written informed consent will be requested. A venous blood sample (3–5 ml) will be collected and G6PD activity measured using UV Spectrophotometry. No follow-up of those participants will be required.

#### Study procedures for the main study

The screening process will be divided over the period of 2 days (Day − 1 and Day 0), and so will be the process of informed consent. This will be done to accommodate for potential delays in receiving the screening results for the G6PD testing. On Day − 1, a brief informed consent will be taken for initial screening tests and if the participant qualified for enrolment, written informed consent will be taken for enrolment into trial purposes. Detailed procedures are listed in Table 1.

Day − 1: All patients coming to the hospital with fever will be screened. For screening purposes, a brief informed consent will be taken and a venous blood sample will be collected. This will be used for malaria RDT, blood film microscopy, quantification of parasite density, dengue NS1 screening and G6PD testing. Women between the ages of 16 to 49 years willing to participate will be asked to take a urinary pregnancy test. A clinical checklist will be used to evaluate the exclusion criteria. Patients who test positive for vivax malaria will receive their first dose of chloroquine.

Day 0: Participants diagnosed with G6PD deficiency will be informed of their status and will be provided with information on the diagnosis and its consequences in everyday life and referred to a regular hospital clinician for treatment. Haemoglobin will be screened using Hemocue™ machine and patients who meet all enrolment criteria and are willing to provide written informed consent will be enrolled into the trial. Following enrolment, a questionnaire will be completed including demographic information, medical history, treatment history, history of recent blood transfusions, and a thorough physical examination will be performed. A venous blood sample will be taken for CBC and LFT. Dried blood spot (DBS) will be made and will be used for subsequent parasite analyses. All participants will receive the second dose of chloroquine under supervision. Patients in both the arms will receive their first dose of primaquine.

Day 1: All participants will be reviewed and the final dose of chloroquine treatment will be provided. Patients in both study arms will receive their second dose of primaquine. Finger prick blood sample will be collected for haemoglobin measurement and microscopy. Physical examination of urine will be conducted.

Day 2: All participants will be reviewed and patients in both arms will receive their third dose of primaquine treatment under observation. Finger prick blood sample will be collected for haemoglobin measurement and microscopy. Physical examination of urine will be conducted.

Days 3–6: Participants in both arms will be treated with primaquine. Home visits will be conducted on alternate days and primaquine doses will be given for that day and the following day for both arms.

Day 7: The study team will visit the participant at home. A brief physical examination will be conducted by a Study Nurse. Finger prick blood sample will be collected for haemoglobin measurement and microscopy. Physical examination of urine will be conducted.

Days 8-13: Participants in the control arm will be treated with primaquine. Home visits will be conducted on alternate days and primaquine doses will be given for that day and the following day for the control arm. No interaction with patients in the intervention arm.

Days 14, 21, and 28 and months 2, 3, 4, 5, and 6: The study team will visit participants at home where they will be reviewed. A brief physical examination will be conducted by the Study Nurse. Finger prick blood sample will be collected for haemoglobin measurement and microscopy.

Unscheduled Visit: All participants with fever or symptoms indicative of malaria will be asked to return to the same health centre as on enrolment. A symptom questionnaire will be completed, a brief physical examination undertaken, and a venous blood sample will be collected and a malaria smear prepared for malaria diagnoses (read immediately) and CBC including haemoglobin and LFT measured. Physical examination of urine will be conducted. In patients with recurrent parasitaemia, DBS will be made and stored for parasite analysis.

Demographics: The patient’s date of birth (or if not known, the estimated age) and gender will be recorded. For screening purposes and if the patient is a female of childbearing age, she will be asked if she is currently pregnant, lactating, planning to get pregnant and the date of the first day of her last menstrual period.

Medical history and physical examination: The details of any disease/surgical conditions, and drug allergies will be recorded. A thorough physical examination will be carried out. The patient’s blood pressure, pulse rate, respiratory rate, height, weight and the results of a baseline physical examination will be recorded. The patient will be checked for pallor and jaundice. This will be done on screening and each subsequent follow-up visit.

Body weight: Body weight will be recorded on day 0/enrolment to the nearest kilogramme (Omron Digital weighing scale). The scales will be calibrated before use. Patients should wear minimal clothing while weighing to avoid overestimation. The screening weight will be used to satisfy the inclusion or exclusion criteria for nutritional status as well as to calculate the dose (number of tablets) to be administered.

Body temperature: Axillary temperature will be checked with a thermometer (Hicks digital thermometer) having a precision of 0.1 °C. Temperature will also be measured as clinically indicated. If the result is < 36.0 °C, the reading will be repeated. Axillary temperature recording will be used throughout the study.

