### Explanation for the choice of comparators {6b}

All participants in the control arm will be treated with radical cure for acute uncomplicated vivax malaria according to local NCVBDC guidelines [6, 7]: 0.25 mg/kg bodyweight primaquine for 14 days, starting on enrolment (Day 0). If the participant vomits the treatment within 60 min, a repeat dose will be administered. If the patient vomits the second dose, he or she will receive parenteral therapy with artesunate and will be withdrawn from the study. Primaquine treatment will be observed daily on the first 3 days, and then alternatively up to 14 days by home visits by staff. Primaquine will be administered with food, to help reduce gastrointestinal side effects.

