### Intervention description {11a}

Patients in the intervention arm will be treated with a 3 day regimen of chloroquine (total dose 25 mg base/kg) plus primaquine (0.50 mg/kg bodyweight for 7 days). If the participant vomits the treatment within 60 min, a repeat dose will be administered. If the patient vomits the second dose, he or she will receive parenteral therapy with an artemisinin combination therapy (ACT) and be withdrawn from the study. Primaquine treatment will be observed daily on the first 3 days, and then on alternate days up to 7 days by home visits by staff. Primaquine will be administered with food, to help reduce gastrointestinal side effects.

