##### Safety

The proportion of patients vomiting their medication within 1 hour of administration.The proportion of adverse events and serious adverse events.The incidence risk of anaemia (Hb < 8 g/dL) and/or the risk for blood transfusion.Risk of > 25% fall in haemoglobin on any day of treatment.The incidence risk of an acute drop in Hb of > 5 g/dL during primaquine treatment.Gastrointestinal (GI) tolerability — incidence of abdominal pain, heartburn, diarrhoea, constipation, nausea and vomiting.

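### Table 1 shows adverse event collection on days 8–13 for everyone, but the text gives the 7-day arm no contact then, so reported adverse events and GI symptoms may be ascertained unequally

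*Protocol article*

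**What the plan says.** For days 8–13, the protocol article (Study procedures for the main study) says of the 14-day arm: "Home visits will be conducted on alternate days and primaquine doses will be given for that day and the following day for the control arm". Of the 7-day arm it says: "No interaction with patients in the intervention arm". The treatment sections agree. Home visits in the 7-day arm run "then on alternate days up to 7 days by home visits by staff" (Intervention description {11a}), and in the control arm "then alternatively up to 14 days by home visits by staff" (Explanation for the choice of comparators {6b}). The next contact common to both arms after day 7 is day 14, when "The study team will visit participants at home where they will be reviewed".

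Table 1 (Participant timeline {13}) has an AE/SAE row marked in every column from enrolment to month 6, including day 8–13. The row names no arm. The table does separate the arms for primaquine, for example in the row "7 day arm PQ 0.50 mg/kg BW". The procedures section defers to this table: "Detailed procedures are listed in Table 1".

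The safety outcomes (Outcomes {12}, Safety) include the proportion of adverse and serious adverse events and GI tolerability, defined as "incidence of abdominal pain, heartburn, diarrhoea, constipation, nausea and vomiting". Neither is limited to dosing days. The Safety analysis section counts subjects with an event, not events.

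**The concern.** AE/SAE is the only procedure marked in the day 8–13 column, and in one arm there is no scheduled occasion on which to carry it out. Adverse event reporting and harms {22} makes the investigator or site staff responsible for detecting events, so what is recorded depends partly on how often staff see the patient. The trial is open label.

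Because subjects are counted once for a given event, a symptom picked up only at an extra home visit adds a person to the control numerator. The same symptom in a 7-day patient is recorded only if it is remembered at day 14 or reported spontaneously. The unscheduled visits described are for fever or symptoms suggesting malaria, so a passing GI complaint need not prompt one.

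Comparing the safety and tolerability of the two regimens is a named objective, and the results are meant to inform national policy. If part of a tolerability advantage for the shorter course came from less frequent enquiry, the reported data could not separate that part from the regimen's own effect.

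**Working it through.** **1. The places side by side, days 8–13**

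| Place | 14-day arm | 7-day arm |
|---|---|---|
| Table 1, AE/SAE row | marked | marked (no arm distinction) |
| Study procedures | alternate-day home visits | no contact |
| Sections {6b} and {11a} | home visits to day 14 | home visits to day 7 |

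Scheduled collection in the 7-day arm is therefore impossible if the text is followed.

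**2. Scheduled contacts, days 0–14**

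- Common to both arms: days 0, 1 and 2 (3), two alternate-day visits within days 3–6 (2), day 7 (1), day 14 (1). Total 3 + 2 + 1 + 1 = 7.
- Control arm only: three alternate-day visits within days 8–13.
- Totals: 7 in the 7-day arm and 7 + 3 = 10 in the 14-day arm. The totals are the same whether the alternate days are 3, 5, 8, 10, 12 or 4, 6, 9, 11, 13.

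**3. How large an artefact could be**

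The protocol states no adverse event rate, so this is an illustration on assumed inputs. Let r be the risk of a recorded event outside days 8–13, q the true risk within days 8–13 (set equal in both arms), and s the share of days 8–13 events that the 7-day arm recovers at day 14. All days 8–13 events in the control arm are taken as found.

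- Control: 1 − (1 − r)(1 − q)
- 7-day arm: 1 − (1 − r)(1 − qs)
- Difference, 7-day minus 14-day: −(1 − r) × q × (1 − s)

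With r = 20% (assumed), q = 10% and s = 50%, control is 1 − 0.8 × 0.90 = 28% and the 7-day arm is 1 − 0.8 × 0.95 = 24%. The difference is −4 points with no true difference between arms. The range, in percentage points:

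| q | s = 0 | s = 50% | s = 80% | s = 100% |
|---|---|---|---|---|
| 5% | −4 | −2 | −0.8 | 0 |
| 10% | −8 | −4 | −1.6 | 0 |
| 20% | −16 | −8 | −3.2 | 0 |

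Under this model the artefact never favours the 14-day arm, and it vanishes when enquiry is equally complete in both arms.

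**4. Which outcomes can be affected**

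Scheduled haemoglobin is measured on the same days in both arms (0, 1, 2, 7, 14, 21, 28, then monthly), so this gap does not touch the haemoglobin endpoints. Vomiting within 1 hour of a dose can occur only on dosing days. That leaves reported adverse events and GI symptoms.

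**The case against.** **Control-only collection is not stated.** A reader might infer that the plan collects adverse events on days 8–13 in the control arm only. The text describes those visits as dosing visits, and the adherence section {11c} mentions only watching the dose and asking about the previous day's. Enquiry about adverse events there is inferred from the Table 1 mark. The row could also denote continuous surveillance rather than a visit procedure. This stands as a limit, so the conclusion is conditional. It does not remove the conflict, because the text names Table 1 as the list of procedures and the row does not exempt the 7-day arm.

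**A fixed gap cannot be claimed.** A reader might give every contact an independent 2–5% chance of recording an event, obtaining 1 − 0.98^7 = 13.2% against 1 − 0.98^10 = 18.3%, or 1 − 0.95^7 = 30.2% against 1 − 0.95^10 = 40.1%, and conclude that there is a spurious gap of 5–10 points. That treats contacts as generating events and ignores recovery at the shared day 14 visit. The document supports neither the rate nor the model.

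**The whole safety comparison is not biased.** Every safety outcome named in the abstract concerns haemoglobin or transfusion.

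**A control excess may be real.** The 7-day course is dosed on days 0–6 and both arms are seen on day 7, so the gap covers days when only the control arm is on drug. This stands. It is also why unequal enquiry is awkward: a drug effect and a detection effect would appear in the same days and the same arm.

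**Safety is only described, with no formal test stated.** True, but the objective is comparative, and readers will compare descriptive proportions by arm.

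**Conclusion.** The conflict between Table 1 and the procedures text is certain, as is the contact count: 3 against 0 on days 8–13 and 10 against 7 over days 0–14. Unequal ascertainment follows if adverse events are asked about at the control home visits, which Table 1 implies but the text does not say. Its direction would favour the 7-day arm. Its size is not computable from the protocol: zero with full recall at day 14, and between −0.8 and −16 points over the assumed values with incomplete recall. Those figures rest on equal true risk in both arms on days 8–13, which may not hold while controls are still taking primaquine. The point is confined to reported adverse events and GI symptoms. It is worth correcting because the remedy is cheap, but it does not undermine the efficacy comparison or the haemoglobin safety endpoints.

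**What to change.** 1. Reconcile the AE/SAE row of Table 1 for days 8–13 with the procedures text, and state whether adverse events are asked about at the control arm's home visits.
2. At the existing day 14 visit, ask both arms the same symptom question covering days 8–14.
3. Present the between-arm adverse event and GI comparison on events elicited at contacts common to both arms, alongside the all-events summary. Flag events found only at control visits on days 8–13; do not exclude them, because they arise during treatment with the longer regimen and dropping them could understate its burden.

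The cost is one CRF prompt and one extra table, with no new visit. Recruitment began on 11/9/23 and was expected to finish in March 2024, so participants already past day 14 will not have had the prompt and elicitation will be mixed. Report that as a limitation, together with the number of scheduled contacts by arm.
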